**Secondary Objectives;**

## To validate use of the cervical collar device as an enhancement for quantitative measurement of thyroid uptake in patients after diagnostic I-123 and low dose I-131 in Graves disease

## To validate use of the cervical collar device as an enhancement for quantitative measurement of thyroid uptake in patients after therapeutic I-131 for thyroid remnant ablation in thyroid cancer.

## To obtain detailed early-phase thyroid uptake data using a cervical collar device in the Graves disease and thyroid cancer patients as described above.

1. **Background**

Radioiodine treatment for thyroid disorders represented an early example of individualized medicine. Since its introduction 80 years ago, the therapeutic I-131 dosage has usually been tailored to individual patient requirements based on the uptake of a tracer radioiodine dose . Various techniques have been employed to estimate the administered dose of I-131 for optimal therapeutic benefit . Estimated exposure has typically been extrapolated from the results of activity measurements at one or two time points, e.g., at 4 and 24 hours . We now know that treatment of hyperthyroid Graves disease with these methods lead to a 13-25% rate of failure to cure hyperthyroidism and a 46-80% rate of long-term hypothyroidism in cured patients . Similarly, such relatively crude dosimetry doubtless result in significant overtreatment in the case of remnant ablation for differentiated thyroid cancer.For patients with differentiated thyroid cancer requiring remnant ablation, the administered activity has, in most cases, been derived empirically, ranging between 30-100 mci . The high success rates in ablating remnant thyroid tissue implies that many patients are still treated with higher 131-I doses than required, with potential side effects, such as radiation sialadenitis.

1. **Study Procedures**

This will be an unmasked prospective pilot study involving patients with Graves disease (Group I) and differentiated thyroid cancer (Group II). Five patients in each group will have radiation activity measurements using the COTI devise. All persons in the study will receive 131-I treatment based on the current standards of care for dose estimation.

**Study Device;**

The CoTI has 3 components;(Image below)

- A collar unit: a gamma detector wrapped around a body part-neck in this case and contains a scintillating crystal and a silicon photomultiplier. The photon pulse signal is then converted to digital signals (measuring the counts per second). Usually two detectors are placed in specified positions.

- A cable that connects the collar unit to the Control Unit

- A control unit that collects the signals and transmits it wirelessly to a hand-held computer tablet.

Two types of collar devices will be used: the lower activity and the medium activity

1. Lower activity collar for patients with Graves disease as well as diagnostic I-123 scan in thyroid cancer patients. These patients typically receive 0.2-1.2 m Ci of I-123/I-131.
2. Medium activity collar for Patients with thyroid cancer after 131-I ablation, for which patients typically receive 30-100 mci of I-131.

Figure 1.

[figure not shown]

**Study Population;**

- Group I (A,B): Patients with diffuse toxic goiter (Graves disease) diagnosed clinically with no prior history of radioiodine treatment.
- Group II (C ): Patients with differentiated epithelial thyroid cancer who are s/p total thyroidectomy and candidates for remnant ablation based on ATA guidelines.

**IRB approval and HIPPA regulations;**

Since it is a project involving a medical device which will be applied to the patients’ neck, it will require the following;

1. IRB regular approval.
2. Registry into the clinicaltrials.gov.
3. Appropriate forms and consent process for the patients.

**The recruitment of subjects for the study;**

- Informed consent including the benefits and the risks of the Collar device (CoTI) will be obtained.
- There will be separate consent forms for Graves disease and Thyroid Cancer
- Demographic, clinical and laboratory data of the participants will be obtained, as outlined below at the time of placement of the coTI The instructions on the application CoTI will be provided in detail.

Patients would be provided with contact information in the event of any discomfort or challenges while applying the device

Patients would be provided with contact information in the event of any discomfort or challenges while applying the device

The scheduled list of procedures is outlined for the study participants:

1. Group I(A)-Graves disease (I-123 scan)- Table A
2. Group I(B)-Graves disease (I-131 scan)-Table B
3. Group II(C )-Thyroid Cancer (I-131 scan)-Table C

The schedule is at the end of the protocol

**FDA Approval and requirements;**

***The study would qualify for the Investigational Drug Exemption (IDE) regulations based on the published FDA criteria:***

[https://www.fda.gov/MedicalDevices/DeviceRegulationandGuidance/HowtoMarketYourDevice/InvestigationalDeviceExemptionIDE/ucm046164.htm#pre_ide](https://www.fda.gov/MedicalDevices/DeviceRegulationandGuidance/HowtoMarketYourDevice/InvestigationalDeviceExemptionIDE/ucm046164.htm" \l "pre_ide)

CoTI device doesn't deliver energy to the patient nor generate excessive heat. The LoHi detectors will warm up a bit (~30°C/86°F) if  forced on constantly, as in during safety testing, but remain just a few degrees above room temperature in normal use (as per the AG Medical Safety assessment)

**Preparing the patient;**

**Group I (A)-Graves Disease**

The patients will be prepared by general standards of care prior to CoTI placement. For patients with Graves disease (Group IA), any thionamide antithyroid meds will be stopped 3-5 days prior to I-123 diagnostic dose administration (according to the current standard of care). After obtaining written consent, a venous blood sample will be obtained for work for requisite laboratory evaluation for baseline labs(standard of care procedures), as outlined below, and in women, for a serum pregnancy test. A low activity CoTI device will be placed under supervision and then adjusted for comfort and optimal activity measurement as a trial and then removed. Background activity of the patient, a phantom, and the device itself will be measured. After administration of I-123, an initial uptake at time 0 will be obtained. Anatomical localization of the CoTI in all patients will be standardized by identification of the cricoid cartilage, the thyroid cartilage as well as the suprasternal notch.The CoTI device will then be placed and the patient will be asked to return to the clinic at scheduled imaging times for Table A.

**Group I (B) - Graves Disease**

The patients will be prepared by general standards of care prior to CoTI placement. For patients with Graves disease, any thionamide antithyroid meds will be stopped 3-5 days prior to I-131 (0.2 mci) diagnostic dose administration. After obtaining written consent, a venous blood sample will be obtained for work for requisite laboratory evaluation for baseline labs(standard of care procedures), as outlined below, and in women, for a serum pregnancy test. A low activity CoTI device will be placed under supervision and then adjusted for comfort and optimal activity measurement as a trial and then removed. Background activity of the patient, a phantom, and the device itself will be measured. Anatomical localization of the CoTI in all patients will be standardized by identification of the cricoid cartilage, the thyroid cartilage as well as the suprasternal notch in patients with Graves disease, who will be administered 200 µCi of I-131 and fitted with a low-activity CoTI device after administration of the dose. Background activity of the patient, a phantom and the device itself will be measured prior to placement of the device. After administration of I-131, an initial uptake at time 0 will be obtained. The CoTI device will then be placed and the patient will be asked to come back at scheduled imaging times for Table B.

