There are no penalties for completing the protocol except that the gift cards will have to be returned back.

1. **Costs**
2. Detail costs of study procedure(s) or drug (s) or substance(s) to participants and identify who will pay for them.

The study is being funded by a small grant received by the Thyroid Tumor Center (under the stewardship of [name]) that is a subsidiary of the Division of Endocrinology, Department of Medicine, Johns Hopkins Hospital.

|  |  | ***Run-***  ***Up-days***  ***0*** | ***Day 0***  ***9.00 am*** | ***Day 0***  ***3 pm*** | ***Day 1***  ***9 am*** | ***Follow up***  ***Day***  ***7*** |
| --- | --- | --- | --- | --- | --- | --- |
|  |  | ***-4 ± 1*** |  |  |  |  |
| ***Stop anti-thyroid meds*** | | ***X*** |  |  |  |  |
| ***I-123 dose*** | |  | ***X*** |  |  |  |
| ***COTI measurement*** | |  | ***X0*** | ***X0*** | ***X0*** |  |
| ***Uptake Measurement by probe (SOC)*** | |  | ***X*** | ***X*** | ***X*** |  |
| ***I-123 Planar scan*** | |  |  | ***X*** |  |  |
| ***Informed Consent*** | |  | ***X0*** |  |  |  |
| ***Review Eligibility*** | |  | ***X0*** |  |  |  |
| ***Medical History*** | |  | ***X*** |  |  |  |
| ***Physical Exam*** | |  | ***X*** |  |  |  |
| ***Vital Signs*** | |  | ***X*** |  |  |  |
| ***Clinical Labs*** | |  | ***X*** |  |  |  |
| ***Pregnancy Test-eligible*** | |  | ***X*** |  |  |  |
| ***Place Collar*** | |  | ***X0*** |  |  |  |
| ***Give instructions*** | |  | ***X0*** |  |  |  |
| ***Questionnaires*** | |  | ***X0*** |  |  |  |
| ***Adverse Events*** | |  | ***X0*** |  |  |  |
| ***Concomitant***  ***Medications*** | |  | ***X0*** |  |  |  |

***Table A Schedule of Visits after 123 dose for Graves disease Patients – All the visits marked with superscript (o)are part of research-Imaging schedule after I-123 dose***

|  | ***Visit***  ***No.*** | ***Run-***  ***up***  ***0*** | ***Day***  ***0***  ***9 am*** | ***Day***  ***1***  ***9 am*** | ***2***  ***9***  ***am*** | ***3***  ***9***  ***am*** | ***4***  ***9***  ***am*** | ***5*** | ***6*** | ***Follow-***  ***up***  ***7***  ***9am*** |
| --- | --- | --- | --- | --- | --- | --- | --- | --- | --- | --- |
| ***Activity*** | ***Days*** | ***-4 ± 1*** | ***0*** | ***1*** | ***2*** | ***3*** | ***4*** | ***5*** | ***6*** |  |
| ***Stop thionamide***  ***anti-thyroid meds*** | | ***X**** |  |  |  |  |  |  |  |  |
| ***I-131 200 µ administration*** | |  | ***X**** |  |  |  |  |  |  |  |

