| ***Uptake Measurement*** | |  | ***X**** | ***X**** |  |  |  |  |  |  |
| ***Informed Consent*** | |  | ***X**** |  |  |  |  |  |  |  |
| ***Review Eligibility*** | |  | ***X**** |  |  |  |  |  |  |  |
| ***Medical History*** | |  | ***X**** |  |  |  |  |  |  |  |
| ***Physical Exam*** | |  | ***X**** |  |  |  |  |  |  |  |
| ***Vital Signs*** | |  | ***X**** |  |  |  |  |  |  |  |
| ***Clinical Labs*** | |  | ***X**** |  |  |  |  |  |  |  |
| ***Pregnancy Test*** | |  | ***X**** |  |  |  |  |  |  |  |
| ***Place Collar*** | |  | ***X**** |  |  |  |  |  |  |  |
| ***Give instructions*** | |  | ***X**** |  |  |  |  |  |  |  |
| ***Questionnaires*** | |  | ***X**** | ***X**** |  |  |  |  |  |  |
| ***SPECT $*** | |  | ***X* 3pm*** | ***X**** | ***X**** | ***X**** |  |  |  |  |
| ***COTI measurement$*** | |  | ***X* 3pm*** | ***X**** | ***X**** | ***X**** | ***X**** |  |  |  |
| ***Low dose CT for attenuation correction*** | |  |  | ***X**** |  |  |  |  |  |  |
| ***Adverse Events*** | |  | ***X**** | ***X**** |  |  |  |  |  |  |
| ***Medications*** | |  | ***X**** | ***X**** |  |  |  |  |  |  |

***Table B- Imaging schedule for Graves disease low dose I-131 scan, COTI measurement and SPECT CT at 3 pm that day-The schedule marked with superscript are part of the research.This is a research scan.***

| ***SCHEDULE OF PROCEDURES*** | | | | | | | | | | | |
| --- | --- | --- | --- | --- | --- | --- | --- | --- | --- | --- | --- |
|  | ***Visit***  ***No.*** | ***Run-***  ***up***  ***0*** | ***Day***  ***1***  ***Time***  ***9.00 am*** | ***2***  ***9***  ***am*** | ***3***  ***9 am*** | ***4***  ***9 am*** | ***5***  ***9***  ***am*** | ***6*** | ***7*** | ***8*** | ***Day***  ***11*** |
| ***Activity*** | ***Days*** | ***-4 ± 1*** | ***0*** | ***1*** | ***2*** | ***3*** | ***4*** | ***5*** | ***6*** | ***7*** |  |
| ***Low iodine diet*** | | ***-14 +/-1 day*** |  |  |  |  |  |  |  |  |  |
| ***Informed Consent*** | |  | ***X*** |  |  |  |  |  |  |  |  |
| ***Review Eligibility*** | |  | ***X1*** |  |  | ***X1*** |  |  |  |  |  |
| ***Medical History*** | |  | ***X1*** |  |  |  |  |  |  |  |  |
| ***Physical Exam*** | |  | ***X1*** |  |  |  |  |  |  |  |  |
| ***Vital Signs*** | |  | ***X1*** |  |  | ***X1*** |  |  |  |  |  |
| ***Clinical Labs*** | |  | ***X1*** |  |  |  |  |  |  |  |  |
| ***Pregnancy Test*** | |  |  | ***X1*** |  |  |  |  |  |  |  |
| ***Thyrogen Injection*** | |  | ***X1*** | ***X1*** |  |  |  |  |  |  |  |

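### Table B stops thionamides 3 to 5 days before informed consent and eligibility review, for a scan labelled research

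*Protocol*

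**What the plan says.** The Protocol's section on preparing the patient, Group I (B), describes the run-up to the 200 µCi I-131 tracer: "any thionamide antithyroid meds will be stopped 3-5 days prior to I-131 (0.2 mci) diagnostic dose administration. After obtaining written consent", after which blood is drawn and the collar is fitted. The paragraph opens with a general statement: "The patients will be prepared by general standards of care prior to CoTI placement".

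Table B turns this into a schedule. The thionamide stop is in the run-up column, day -4 ± 1. Informed Consent and Review Eligibility are each entered once, on Day 0, the day of the I-131 dose, and their run-up cells are empty. Adverse Events starts on Day 0. The caption reads: "The schedule marked with superscript are part of the research.This is a research scan". The stop carries that research mark.

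The parallel text for the I-123 scan, Group I (A), is more explicit. There, thionamides "will be stopped 3-5 days prior to I-123 diagnostic dose administration (according to the current standard of care"), and Table A leaves the stop without a research mark.

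**The concern.** Consent and eligibility review should come before anything done to a patient for research. Table B reverses this: a patient on thionamides comes off them, and only 3 to 5 days later is asked for consent and checked against the exclusion criteria. The stop is timed to a tracer dose given for a scan that the caption calls research.

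Three things are at stake.

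- **Consent.** If the stop is a research step and no consent has been given earlier, active treatment is withdrawn without agreement.
- **Eligibility.** Cervical spine disease and iodinated contrast within 8 weeks are exclusions that can be checked in advance. As scheduled, an ineligible patient would find out only after several days off treatment for a scan that cannot go ahead.
- **Safety.** The Study Statistics section lists rebound hyperthyroidism after stopping antithyroid drugs as an early stopping reason. Table B schedules no adverse-event check during the run-up, when it could begin. Symptoms in that interval enter the scheduled record only if they are reported on Day 0 or later.

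**Working it through.** **1. The interval.** Inputs are from Table B: stop at day -4 ± 1; consent, eligibility review and I-131 dose on Day 0.

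- Earliest stop: -4 - 1 = day -5, so the gap is 0 - (-5) = 5 days.
- Latest stop: -4 + 1 = day -3, so the gap is 0 - (-3) = 3 days.

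The gap is 3 to 5 days, which matches the interval in the Group I (B) text. Text and table agree on when the drug stops. Table B is what fixes consent after it.

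**2. Is the stop research or routine care?** The relevant places, side by side:

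| Place | What it indicates |
|---|---|
| Group I (A) text (I-123) | Stop is standard of care |
| Table A | Stop row has no research mark |
| Group I (B) text (I-131) | General standard-of-care opening; the stop sentence has no such label |
| Table B | Stop row has the research mark; caption calls the scan research |

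The mark in Table B cannot decide the matter. Counting rows that carry a research mark:

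- Table B: 18 of 18, including Clinical Labs, which the Group I (B) text calls standard of care.
- Table A: 8 of 17, with neither the stop nor Clinical Labs among them.

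A mark on every row does not separate research from care. The status of the I-131 stop therefore stays open.

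**3. Could consent already have been given?** The recruitment section separates consent forms by disease only, so one Graves form may cover both scans. The order of I(A) and I(B) is not stated. A patient who went through Table A first would have consented on its Day 0. Table B nevertheless schedules its own consent and eligibility review on Day 0 and does not refer to an earlier one.

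**4. How many patients?** Study Procedures gives five patients in Group I.

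| Situation | Withdrawn for research before consent? |
|---|---|
| Not taking thionamides | No |
| Stop is routine care | No, though study eligibility is still reviewed afterwards |
| Stop is research, consent given at Table A | No |
| Stop is research, no earlier consent | Yes, by 3 to 5 days |

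The number on thionamides is not given. The minimum is 0 and the maximum is 5 (all of Group I taking thionamides and in the last row).

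**The case against.** The strongest reply is that the stop is ordinary care. The Group I (B) paragraph opens with a standard-of-care sentence immediately before the stop, and the near-identical Group I (A) paragraph labels the same 3-to-5-day stop that way. One missing parenthesis is weak evidence of a different status. Where the form asks why current therapy would be stopped, the Protocol answers that care follows current standards. Group I patients are likely candidates for I-131 treatment in any case.

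The primary objective can also be read as giving both tracers to the same patients, in which case consent at Table A may come first. The phrase about written consent in the Group I (B) text strictly governs the blood sample, so the narrative alone does not place consent after the stop. Finally, the Data and Safety Monitoring Plan provides for continuous safety monitoring by the investigator.

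Much of this stands as a reason for caution. It is why the lower bound is 0 and why the stop cannot simply be called research. It does not remove the problem. The general answer on stopping therapy does not mention withdrawal for the I-131 tracer. The possible earlier consent is nowhere stated, and Table B schedules a fresh one. The monitoring plan does not say that it covers people who have not yet consented. Even on the routine-care reading, eligibility would still be reviewed only after the drug is off.

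**Conclusion.** The point holds. As written, Table B places consent and eligibility review 3 to 5 days after a drug withdrawal that is timed to a research scan, and no text in the Protocol clearly makes that order acceptable. Between 0 and 5 Group I patients are affected. The upper figure assumes that all five take thionamides, that the stop is a research step, and that none consented earlier at Table A. Sample size and analysis are unaffected. This is a question of participant protection and should be fixed before patients are scheduled under Table B. Confidence is medium, because the status of the stop and the order of the two Graves scans are not given.

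**What to change.** In Table B, move Informed Consent and Review Eligibility from Day 0 to the run-up column, ahead of the thionamide stop. For a stop on day -5, that means by day -5. Add an Adverse Events entry in the same column. If patients are meant to pass from I(A) to I(B) under one Graves consent, say so in a footnote to Table B.

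Two clerical corrections go with this: state in the Group I (B) text whether the I-131 stop is standard of care, and limit Table B's research mark to rows that are research, so that text and tables agree. The medication rule itself and the Day 0 pregnancy test can stay as they are.

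The cost is a schedule and wording amendment and one earlier contact with the patient, 3 to 5 days before Day 0.

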**Group II ( C )- Thyroid Cancer**

Patients with differentiated thyroid cancer will be placed on a low iodine diet for two weeks as per standard of care. Recombinant TSH will be administered on days 1 and 2 (typically Monday and Tuesday), and the diagnostic I-123 dosage will be administered on day 2, as per standard of care. The diagnostic whole-body scan is done on day 3 and the I-131 dose for I-131 ablation (30-100 mci)is administered on day 4, as per standard of care.
After obtaining written consent, venous blood sample will be obtained for work for requisite laboratory evaluation for baseline labs as outlined below, including in women, a pregnancy test prior to the I-131 remnant ablation dose.These are standard of care procedures. The (low to medium activity) CoTI device will be placed under supervision and then adjusted for convenience as outlined above. Background activity of the patient, a phantom, and the device itself will be measured. After administration of I-131, an initial uptake at time 0 will be obtained. Anatomical localization for the CoTI for all patients will be standardized by identification of the cricoid cartilage, the thyroid cartilage as well as the suprasternal notch.The CoTI device will then be placed and the patient will be asked to come back at scheduled imaging times for Group II(Table C).

**Scheduled Imaging times (Tables at the end);**

**Group I (A) - Persons with Graves disease**

After I-123 diagnostic dose;

- An uptake at 0 hours -for background at 9 am

- A planar image with a pinhole collimator at time 06.00 hours with an uptake at the same time.

- An uptake only measurement (with the probe) at time 24.00 hours.

- The counts from the handheld device connected to the CoTI would be obtained at similar times i.e. 0, 6 and 24 hours.The total duration of each visit would be an hour.

**Group I (B) --Persons with Graves disease**

After administration of 200 µCi of I-131 dose;

- A first SPECT image would be performed at 6 hours after I-131 dose.

-A Second SPECT image (with a low dose CT for quantification and attenuation correction) would be performed at 24 hours after I-131 dose.

-A third SPECT image at 48 hours.

-A fourth SPECT image at 72 hours.

- The counts from the handheld device connected to the CoTI would be obtained at similar times as above with one additional time point of 96.00 hours i.e. 6, 24, 48, 72 and 96.

**Group II - Persons with Thyroid Cancer**

- A SPECT image would be performed at 24 hours (with low dose CT for quantification and attenuation correction) after I-131 therapy.

- A second SPECT image at 48 hours.

- A third SPECT image at 72 hours (with low dose CT for quantification and attenuation correction).

A final SPECT CT image (with low dose CT for quantification and attenuation correction) at day 7 post therapy.

- The counts from the handheld device connected to the CoTI would be obtained at similar times as above with one additional time point of 96.00 hours i.e. 24, 48, 96 and day 7.

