## Primary Objective;

To perform a pilot (exploratory) study using a novel AG Medical Collar Therapy Indicator (CoTI) to evaluate the variability in radioiodine kinetics across patients treated for hyperthyroid Graves disease and postoperative thyroid remnant ablation for thyroid cancer.

- - For Graves disease, after administration of 0.2 mci I-123 and low dose (200 µCi) I-131, to compare conventional 6, 24, 48 and 72-hour fractional thyroidal radioiodine uptakes with single photon emission (with low-dose computed tomography [SPECT/CT] for quantification and attenuation correction) with the activity measured continuously by the COTI device, which is placed in collar around the neck resembling a turtle neck sweater collar with a wire and recording box.
  - For remnant ablation, after therapeutic administration of 30 mCi I-131, to compare conventional 24, 48, 72 hr. and 7-day SPECT (with low dose CT for quantification and attenuation correction performed at 24, 48, 72 hours and 7 days) with the activity continuously measured by the COTI device, as described above.

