| ***Diagnostic I-123 dose (1 pm)*** | |  |  | ***X1*** |  |  |  |  |  |  |  |
| ***Diagnostic WBS (11 am)*** | |  |  |  | ***X1*** |  |  |  |  |  |  |
| ***I-131 30 mci (1PM)*** | |  |  |  |  | ***X1*** |  |  |  |  |  |
| ***Give instructions*** | |  | ***X1*** |  |  |  |  |  |  |  |  |
| ***Questionnaires*** | |  | ***X1*** |  |  |  |  |  |  |  |  |
| ***COTI placement*** | |  |  |  |  | ***X*** |  |  |  |  |  |
| ***COTI measurement*** | |  |  |  |  | ***X*** | ***X*** | ***X*** | ***X*** | ***X*** | ***X*** |
| ***SPECT*** | |  |  |  |  |  | ***X*** | ***X*** | ***X*** |  | ***X1*** |
| ***Low dose CT for attenuation*** | |  |  |  |  |  | ***X*** |  | ***X*** |  | ***X1*** |
| ***Review of Risks***  ***Benefits*** | |  | ***X*** |  |  |  |  |  |  |  |  |
| ***Adverse Events*** | |  | ***X1*** | ***X1*** |  | ***X1*** |  |  |  |  |  |
| ***Concomitant***  ***Medications*** | |  | ***X1*** | ***X1*** |  | ***X1*** |  |  |  |  |  |

***Table C -Thyroid Cancer Patients-The events not marked with a superscript 1 are part of research. The events in red are part of research protocol. Imaging and visit schedule for thyroid cancer***

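### The Group II list of CoTI read-out times omits 72 h, contradicting its own rule, the primary objective and Table C

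*Protocol*

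**What the plan says.** The Group II part of the protocol's Scheduled Imaging times section sets SPECT at 24, 48 and 72 h and day 7, with low-dose CT at 24 h, 72 h and day 7. The 72 h scan reads: "A third SPECT image at 72 hours (with low dose CT for quantification and attenuation correction". The collar rule follows: "The counts from the handheld device connected to the CoTI would be obtained at similar times as above with one additional time point of 96.00" (in h). The times are then spelled out as "with one additional time point of 96.00 hours i.e. 24, 48, 96 and day 7".

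Three other places bear on this:

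- **Primary Objective, remnant ablation bullet.** The comparison is "to compare conventional 24, 48, 72 hr. and 7-day SPECT" against the collar. CT is described as "performed at 24, 48, 72 hours and 7 days) with the activity continuously measured by the COTI device".
- **Table C.** The CoTI measurement row is marked in day columns 4, 5, 6, 7, 8 and 11. The SPECT row is marked in columns 5, 6, 7 and 11. I-131 is given in column 4.
- **Group I (B) imaging times.** The parallel sentence, "The counts from the handheld device connected to the CoTI would be obtained at similar times" to the scans plus 96 h, lists 6, 24, 48, 72 and 96 h, so 72 h is kept.

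On continuity, the third secondary objective is "To obtain detailed early-phase thyroid uptake data using a cervical collar device" in both diseases. The Study Device section says that the control unit collects the signals and sends them to a tablet. No section gives a logging interval, or says that the record between visits is stored and retrieved.

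**The concern.** The sentence that tells staff when to take Group II collar readings gives a rule and a list that disagree. The list leaves out a time at which the reference scan is done with CT, and keeps 96 h, which has no scan and so cannot form a pair.

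The primary objective for this group is a comparison of collar and SPECT at matched times, in five patients. The planned analysis is a Spearman correlation between collar and conventional measurements. A reading missed at 72 h removes one point of that comparison in every patient treated under the list, and one of the better-quantified ones.

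A smaller matter sits beside this. The case for the collar rests on continuous measurement and the full time-activity curve. The imaging sections state when counts are obtained from the handheld device, but not what happens to the signal in between.

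**Working it through.** The protocol gives no sample-size, power or alpha figure to reproduce here. The check is a comparison of sets of times.

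**Inputs** (day 7 = 7 × 24 = 168 h)

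| Item | Source | Times (h) |
|---|---|---|
| SPECT | Group II imaging times | 24, 48, 72, 168 |
| Low-dose CT | Group II imaging times | 24, 72, 168 |
| SPECT to be compared | Primary Objective | 24, 48, 72, 168 |
| CoTI, printed list | Group II imaging times | 24, 48, 96, 168 |
| Patients per group | Study Procedures | 5 |

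**Step 1: apply the sentence's own rule.** SPECT times plus 96 h = {24, 48, 72, 96, 168}, five times. The printed list has four. Rule minus list = {72}. Nothing else differs.

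**Step 2: convert Table C.** Hours after I-131 = (day column − 4) × 24.

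- CoTI, columns 4, 5, 6, 7, 8, 11: 0, 24, 48, 72, 96, 168 h.
- SPECT, columns 5, 6, 7, 11: 24, 48, 72, 168 h.
- CT, columns 5, 7, 11: 24, 72, 168 h.

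These hours are nominal. Table C gives the dose at 1 PM and heads column 5 with 9 am, which would be 20 h rather than 24 h. That does not change which columns are marked. Table C minus the printed list = {0, 72}.

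**Step 3: count matched CoTI/SPECT pairs.**

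- Table C: {24, 48, 72, 168}, 4 per patient, 4 × 5 = 20.
- Printed list: {24, 48, 168}, 3 per patient, 3 × 5 = 15.
- Loss: 5 of 20, or 25%.

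**Step 4: count pairs with CT on the same day.** On the CT schedule shared by the Group II imaging section and Table C:

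- Table C: {24, 72, 168}, 3 × 5 = 15.
- Printed list: {24, 168}, 2 × 5 = 10.
- Loss: 5 of 15, or one third.

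The Primary Objective also places CT at 48 h, which the other two places do not. On that schedule CT-corrected pairs would go from 4 × 5 = 20 to 3 × 5 = 15. Either way, 72 h is a CT time.

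**Step 5: early readings.** The printed Group II list has nothing before 24 h. Table C adds one reading on the dosing and placement day. In Graves disease, Group I (A) has CoTI counts at 0, 6 and 24 h, and Group I (B) starts at 6 h.

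**The case against.** The strongest reply is that this is a slip with an obvious reading. The rule in the same sentence, the primary objective, Table C and the parallel Group I (B) list all point to 72 h, and only one enumeration misses it. The Group II preparation text sends patients back at the imaging times of Table C, so Table C is arguably the governing schedule. All of that stands. It makes the loss conditional, and it makes this an inconsistency rather than a design choice. It does not remove the point: the defective list sits in a section that staff would work from, and nothing says that Table C prevails over it.

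A reader might go further and infer that collar counts are taken only at visits. On that view the early-phase objective has no data source and the advantage of continuous measurement cannot be tested. The protocol does not support this:

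- The imaging sections never say that readings are confined to visits. They are compatible with reading, or matching, a continuous record at the imaging times.
- The Abstract, the Primary Objective and the device rationale all describe continuous measurement. The preparation sections have the patient leave wearing the collar and return for imaging.
- Group I (A) has scheduled counts at 0 and 6 h, so early data in Graves disease exist even on the narrowest reading.

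What remains is that storage and use of the between-visit signal are not stated. That is an operational detail to clarify, and it would not carry a finding by itself.

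**Conclusion.** The Group II CoTI list is wrong as printed. It contradicts the rule in its own sentence, the primary objective and Table C by omitting 72 h.

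The consequence is conditional. If the list were followed, one of four matched times per patient would be lost (20 to 15 pairs), and CT-corrected pairs would fall from 15 to 10. If Table C is followed, no pair is lost. The counts assume five patients with complete data, nominal visit times, and the CT schedule of the imaging section and Table C. They are counts of repeated readings within five patients, not of independent observations, so the 25% describes data points rather than a loss of patients.

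The point is small but should be corrected, because the list is an operative instruction and the correction is trivial. The question of continuous recording is a request for clarification only.

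**What to change.** 1. In the Group II imaging times, replace the list so that it agrees with Table C: the placement-day (0 h) reading, 24, 48, 72 and 96 h, and day 7. Restoring 72 h alone would satisfy the sentence's rule but would still leave out the dosing-day reading that Table C schedules.
2. In the same edit, reconcile the CT times: the Primary Objective includes 48 h, while the imaging section and Table C do not.
3. As a clarification, the sponsor should confirm whether the device stores the signal between visits. If it does, state in the imaging sections that this record is retained and used for the time-activity curve and the early-phase objective, with the readings at imaging times serving as the paired points.

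Item 1 costs only wording, since Table C already has the patient scanned and the collar read at 72 h. Item 2 is also wording, unless the sponsor settles on a 48 h CT, which would be an added procedure. Item 3 is wording only if the device stores its signal. The protocol mentions collection and wireless transmission, not storage, so that cost cannot be judged from the document.
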